### Data Collection

The RA, an occupational therapist with 12 years of experience in clinical research, will collect quantitative data and enter them into a secure database. Sociodemographic information will include age, sex, gender, diagnosis, length of time using a wheelchair, previous experience with using a manual wheelchair (where and for which activities), previous wheelchair training, and assistance required for using a manual wheelchair. Assistance will be assessed using the 5-point General Scale for the Extent of Caregiver Assistance scale (5=no assistance/always autonomous, 4=standby assistance only, 3=verbal assistance only, 2=one-person physical assistance, 1=two-person physical assistance, and -0=equipment needed [31]. Additional information will include the propulsion method and wheelchair specifications (frame type, dimensions, tire, and caster size).

### Primary Outcome

Manual wheelchair skills performance (ie, what the person does in their daily life) will be assessed using the Wheelchair Skills Test Questionnaire for Manual Wheelchair Users (WST-Q-M version 5.4.2) [32,33]. The WST-Q-M comprises 30 discrete skills required to move around in a manual wheelchair indoors and in the community. Participants will rate their performance for each of the 30 manual wheelchair skills on a 4-point scale. The root performance question asks, “Could you do this (manual wheelchair skill) in your own setting?” Response options include “yes, very well (3),” “yes, but not well (2),” “yes, with help (1),” “no (0),” and “no part” (NP) with the manual wheelchair. The total percentage WST score is calculated as: total percentage WST performance=sum of individual skill scores/([# of possible skills – # of NP scores – # of testing error (TE) scores] 3) × 100%. Participants will be asked whether the skill represents a training goal (yes, no) to assist with defining the training program. The WST-Q-M can be completed in approximately 15 minutes, has strong psychometric properties in English and French [34,35], and has been used extensively in clinical trials [16]. The WST-Q-M has been validated by the study team for ARSACS [36]. A minimally clinically important difference (MCID) of 20% relative improvement in WST scores (T1 to T2) has been suggested for adults [22]. However, a recent invited commentary by Best and Kirby [37] suggests that the potential clinical significance of much smaller improvements should be considered.

### Secondary Outcomes

Manual wheelchair skills capacity (ie, what a person can do in a standardized environment) will be assessed using the Wheelchair Skills Test (WST) v5.4 for manual wheelchair users [38,39]. Participants will be asked to execute 30 manual wheelchair skills in a standardized environment. They will be scored on a 4-point scale as “advanced pass (3),” “pass (2),” “partial pass (1),” “fail (0),” “NP,” or “TE.” The total percentage WST score is calculated as: total percentage WST capacity score = sum of individual skill scores/([# of possible skills – # of NP scores – # of TE scores] × 3) × 100%. The WST has been validated in adult populations. An MCID of 20% relative improvement in WST scores (T1 to T2) has been suggested for adults [22].

Manual wheelchair use self-efficacy (ie, belief in one’s ability to accomplish specific tasks while using a manual wheelchair) will be assessed using the Wheelchair Use Confidence Scale for Manual Wheelchair Users Short Form (WheelCon-M) [40]. WheelCon-M comprises 21 statements related to confidence using a manual wheelchair in activities and environments, each rated on a scale from 0 (“not at all confident”) to 10 (“completely confident”), producing a total mean score of 0 to 10 [40,41]. Responses will indicate the current level of perceived confidence in 6 areas (ie, navigate the physical environment in a manual wheelchair, perform activities in a manual wheelchair, problem solve, advocate for needs, and manage social situations and emotions). The WheelCon-M has been validated for ARSACS [36].

Manual wheelchair mobility will be measured using actigraphy, collected with a small, noninvasive, and lightweight accelerometer (Actigraph GT3X; Ametris). The Actigraph GT3X contains a multidirectional accelerometer that integrates information about direction and speed to produce an electrical current with variable magnitude and duration, and the electrical current data are stored as activity counts [42]. The time between sampling units (epochs) will be set at 15 seconds [42].

The participants will receive 2 actigraphs after completing the assessments (T1, T2, and T3); one will be worn on their nondominant arm between the elbow and shoulder, and one will be placed on the rear wheel of their manual wheelchair inside a custom-made waterproof packet that will be installed using tie-wraps. Participants will be asked to wear the actigraphs at all times during a 7-day period, except during sleep, bathing/showering, or swimming. They will also be asked to log the exact time the actigraph was put on and taken off each day [43]. The tester will obtain the actigraphs and logs from the participants at the end of the 7-day period (either in person or by postage-paid envelopes that will be provided to the participants). Actigraphy has been validated for evaluating manual wheelchair mobility in adults [44].

### Qualitative Interviews

The participants will complete semistructured individual interviews lasting between 45 and 60 minutes, either in person or online with the RC, after completing the WSTP intervention. The interview guide will be created by the study team using an iterative process following an appropriate framework (eg, International Classification of Functioning, Disability, and Health) [32]. Questions will explore expectations with wheelchair use, previous experiences with using a wheelchair, and perceptions of wheelchair skills training. In addition, we will explore perceptions of the WSTP (dosage, fatigue, training approaches, and usefulness), experiences with manual wheelchair service provision, satisfaction with manual wheelchair use, and social participation. The interview guide will be pilot tested with 1 person with ARSACS and 1 person with MD1. The interviews will be audio recorded.

### Data Analysis

Summary statistics (means, standard deviations, frequencies, and percentages) will be used to describe the sample. Details of adherence and intervention fidelity will be summarized. Assumptions for parametric testing of quantitative data will be verified, and the data will be screened for outliers [45]. An intention-to-treat analysis will be prioritized (with a per-protocol analysis reported depending on adherence and fidelity), and missing data will be addressed using multiple imputation methods for repeated measures of longitudinal data [46].

To address the primary objective, T2 WST performance scores will be compared between the experimental and control groups using ANCOVA or its nonparametric equivalent, with baseline scores used as the covariate. Variance (*R*^2^), statistical significance (95% CI), and effect sizes (partial η^2^) will be assessed using sums of squares methods. Secondary objectives will be evaluated using linear mixed-effect models, which are flexible to explore within-participant mixed/random effects [47].

Post-hoc exploratory analyses will investigate the influence of age, gender, diagnoses (ataxia or dystrophy), and manual wheelchair experience on effect size using linear mixed-effect models. Comparisons between WST-Q-M within-participant change scores for the experimental group (T1-T2) and WST-Q-M within-participant change scores after training in the control group (T2-T3) will be explored using *t* tests. Sensitivity analyses will be conducted on demographic variables (eg, age, sex, gender, and diagnoses) to generate hypotheses and inform future investigations.

A reflexive thematic analysis will be used to explore perceptions of the influence of manual wheelchair training on mobility, participation, and quality of life according to an appropriate framework (eg, International Classification of Functioning, Disability, and Health) [48]. Interviews will be transcribed verbatim, and researchers will familiarize themselves with the data by rereading and relistening to interviews. Using NVivo software (version 14; Lumivero), transcripts will be coded line-by-line. Then, the codes will be grouped into similar ideas, and themes will be developed using an inductive approach. Member checking will be performed with participants throughout data analysis, with the citizen partner actively involved in data interpretation and synthesis to enhance confirmability. Final themes and subthemes will be verified with participants and the research team. To further enhance trustworthiness according to Ahmed (2024) [49], the credibility of data interpretation will be strengthened through triangulation with quantitative data. Quantitative and qualitative data will then be integrated using joint display diagrams to merge, compare, and relate findings to better understand how subjective perceptions align with measured improvements [50]. We will also explore why some participants may experience better outcomes or how people deal with challenges. Additionally, we will remain aware of potential personal biases regarding our perception of the effectiveness of the intervention. Finally, findings on the facilitators and barriers to training may be transferable to individuals with other neuromuscular disorders who share similar symptoms and functional characteristics [49].

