**Objective:**

The primary aim of this study is to evaluate the efficacy of manual wheelchair skills training for safely improving wheelchair performance in people with ARSACS and MD1. The secondary outcomes include exploring the influence of manual wheelchair skills training on skill capacity, use self-efficacy, mobility, and the retention of outcomes 3 months later. We will also qualitatively explore the manual wheelchair training experiences of people with ARSACS and MD1.

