**Methods:**

This study will use a sequential multimethods design, combining a waitlist randomized controlled trial and qualitative interviews. The participants will include adults who have a diagnosis of ARSACS or MD1 who use a manual wheelchair for mobility. Participants will be randomly assigned to the intervention or control group using a 1:1 allocation ratio. The intervention group will receive 5 manual wheelchair skills training sessions (1-2 sessions/week), while the control group will receive no training. Data will be collected at baseline (T1), after the 4-week intervention (or waiting period for the control group; T2), and 3 months after T2 to assess retention (T3). The primary outcome will be manual wheelchair skills performance. Secondary outcomes will include manual wheelchair skills capacity, self-efficacy, and mobility. Semistructured individual interviews will be conducted to explore participants’ expectations regarding manual wheelchair use, past manual wheelchair experiences, and perceptions of manual wheelchair skills training. Quantitative data will be analyzed using analysis of covariance (ANCOVA), controlling for baseline scores, and qualitative data will be analyzed using reflexive thematic analysis.

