## Methods

### Study Design

A sequential multimethods randomized controlled trial (RCT) and qualitative interviews will be used, with the RCT reported according to the CONSORT (Consolidated Standards of Reporting Trials) guidelines [26]. Participants will be randomly assigned to the intervention or control group using a 1:1 allocation ratio. A randomization process with undisclosed block size will be created by a statistician who is not otherwise involved in the project. Given the potential benefits of the intervention already reported in our previous studies [22,23], control group participants will also receive wheelchair skills training following a 4-week control period and postintervention data collection (ie, they will be on a “waitlist” for the wheelchair skills training program and receive no intervention during the study period).

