### Study Procedures

Following enrollment, participants will complete baseline measures (T1) and then be assigned to either the experimental or the control group. An RC will then contact the statistician via telephone or email to obtain the group assignment within 48 hours. The participant will be informed of the group assignments, and the trainer will be given the participants’ contact information to schedule the training sessions and assign the control group. The training will be scheduled after completing the blinded postintervention data collection (T2). In an effort to minimize bias, a research assistant (RA) will be blinded to group allocation and participants will be instructed not to discuss their program with the RA. The RC will also arrange for the blinded follow-up (retention) data collection for all participants 3 months after postintervention data collection (T3). Qualitative interviews will be conducted by the RC by phone or videoconferencing within 7 days of completing the intervention. Given the self-report nature of the primary outcome, the interdisciplinary experience of 3 study investigators with RCTs who are not located at the data collection site, and the involvement of a citizen partner and Muscular Dystrophy Canada in data collection, analysis, and interpretation, a data monitoring committee was not established. Participants in the intervention and control groups will continue to receive usual care (if any) during the study. The trial design describing coordination, testing, and experimental procedures is depicted in Figure 1.

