### Control Group

Participants in the control group will receive the usual care (if any) during a 4-week period. During this time, participants will be considered on a waitlist to receive the WSTP after the completion of the project and may continue or begin any activities provided by therapists or in the community. After completing the T2 evaluations, participants in the control group will complete a target of five 45-minute weekly sessions of the WSTP, delivered by trained personnel as described for the intervention group. While usual care may include some form of manual wheelchair skills training, the evidence suggests that the amount of training received during usual care, according to the Wheelchair Skills Program, is limited [24].

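### Controls are trained between T2 and T3, so T3 has no untrained comparator and the exploratory t test compares training gains measured at different times after training

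*Protocol article*

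**What the plan says.** The abstract (Methods) places the assessments "after the 4-week intervention (or waiting period for the control group; T2), and 3 months after T2 to assess retention (T3"). Study Procedures applies the same clock to both arms: "blinded follow-up (retention) data collection for all participants 3 months after postintervention data collection (T3"). The abstract (Objective) lists "the retention of outcomes 3 months later" among the secondary outcomes, and Data Analysis assigns secondary objectives to linear mixed-effect models.

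On when controls are trained, the Control Group section states: "After completing the T2 evaluations, participants in the control group will complete a target of five 45-minute weekly sessions of the WSTP". Study Procedures also schedules training after the T2 data collection, and Data Analysis treats the controls' T2-T3 change as a change that follows training: "WST-Q-M within-participant change scores after training in the control group (T2-T3) will be explored using" t tests, set against the experimental group's T1-T2 change.

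Two other phrases sit uneasily with that sequence. The Control Group section also says that "participants will be considered on a waitlist to receive the WSTP after the completion of the project", and Study Design says that controls "receive no intervention during the study period".

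**The concern.** A waitlist design keeps an untrained control group only until the waitlist is released. Here that happens at T2. T3 is the only later assessment described, so two quantities that readers will look for are not cleanly available.

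The first is retention. Nobody is untrained at T3, so a difference between arms at T3 cannot show whether the benefit of training lasts.

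The second is replication of the training gain in the control arm, which is the evident purpose of the t test. The two change scores differ in three ways besides the arm: the length of the interval, the time between the end of training and the measurement, and the amount of disease progression that can occur in a progressive condition. A difference in the t test could come from any of these. An absence of difference could reflect two of them cancelling.

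**Working it through.** **Step 1: order of events.** From Study Procedures, Control Group and Data Analysis:

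| | T1 to T2 (about 4 weeks) | T2 to T3 (3 months) | Status at T3 |
|---|---|---|---|
| Experimental | trained | no further training described | trained, about 13 weeks earlier |
| Control | waiting | trained | trained, more recently |

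No assessment directly after the controls' training is described.

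**Step 2: time from the end of control training to T3.** The article gives no figure, so there is none to reproduce. It can be derived:

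3 months = 365.25 / 4 / 7 = 13.04 weeks.

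Delay = 13.04 − start delay − course length.

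Course length: five weekly sessions (Control Group) take 5 calendar weeks, or 4 weeks from first to last session. At the upper rate in the abstract, two sessions a week, they take about 2.5 weeks. The start delay after T2 is not given; 0 to 4 weeks is assumed here.

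| Course length | Start delay 0 | 1 week | 2 weeks | 4 weeks |
|---|---|---|---|---|
| 5 weeks | 8.0 | 7.0 | 6.0 | 4.0 |
| 4 weeks | 9.0 | 8.0 | 7.0 | 5.0 |
| 2.5 weeks | 10.5 | 9.5 | 8.5 | 6.5 |

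The experimental arm's T2 comes directly after its training period. The t test therefore sets a delay of about 0 weeks against roughly 8 weeks (range 4 to 10.5), and a change interval of about 4 weeks against about 13.

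**Step 3: what timing alone could do.** The article gives no retention rate, so this step rests on assumptions. Suppose the immediate gain is identical in both arms and a fraction L is lost linearly by 13 weeks. With the 8-week delay:

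- Control T2-T3 gain = immediate gain × (1 − L × 8/13).
- L = 0.25: shortfall = 0.25 × 8/13 = 15.4% of the gain.
- L = 0.50: shortfall = 0.50 × 8/13 = 30.8% of the gain.

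For an assumed immediate gain of 20 points, controls would appear to gain 3.1 to 6.2 points less although the training worked equally well. With no loss (L = 0) the artefact is zero. If practice after training raised scores, its sign would reverse.

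**Step 4: chance of a misleading test.** Take the article's d = 1.2 as the true immediate effect in both arms, 10 analysed per arm and two-sided α = 0.05, with d scaled to the standard deviation of the change scores (assumed). If controls keep 75%, 50% or 25% of the effect at their T3, the test targets a difference of 1.2 × 0.25 = 0.3, 1.2 × 0.50 = 0.6 or 1.2 × 0.75 = 0.9. It would be significant in 9.7%, 24.6% or 47.8% of trials.

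**Step 5: a better-matched comparison.** Compare control T2-T3 change with experimental T1-T3 change, under the assumptions of Step 3 and a 20-point immediate gain:

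- L = 0.25: control 16.9, experimental 15.0, difference 1.9.
- L = 0.50: control 13.8, experimental 10.0, difference 3.8.

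The artefact falls from 3.1-6.2 to 1.9-3.8 points and changes direction, because about 8 weeks is now compared with about 13. The mismatch is reduced but not removed.

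**The case against.** The strongest reply is that little of weight depends on this. The primary ANCOVA uses T2, when controls are untrained. The t test appears among analyses labelled post-hoc and exploratory. The Discussion concedes that the trial is not powered for secondary outcomes. All of this stands and limits the severity.

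Four stronger readings are tempting, and the document does not support them:

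- **That the trial plans a between-arm test at T3, in which a retained benefit would show as no difference.** No such contrast is stated. The mixed models are described only as suited to within-participant effects, and the choice of contrasts may be left to a fuller document. What stands is that a group contrast including T3 would compare trained with trained, so it is worth ruling out explicitly.
- **That multiple imputation would carry the training effect into the controls' T2 values.** This would need an imputation model without arm-specific time effects. The article does not describe the model, so the inference fails.
- **That Study Design flatly contradicts the Control Group section.** The same Study Design sentence says that controls are trained after the 4-week control period and the data collection that follows it, so its closing phrase can be read as meaning that period. The Control Group phrase about completion of the project cannot be read that way and does conflict.
- **That the bias has a known size and direction.** The decay rates and the 20-point gain are assumptions. The Primary Outcome section gives its 20% as a relative improvement, not as points. Continued practice could push the other way.

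The fact of the confounding survives. It follows from the stated schedule and the stated comparison, and it does not depend on any detail the article leaves out.

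**Conclusion.** The point holds at moderate severity. On the sequence that Data Analysis itself assumes, T3 offers no trained-versus-untrained comparison. The stated t test confounds arm with interval length (about 4 against about 13 weeks) and with time since training (about 0 against roughly 8 weeks, or 4 to 10.5 under the assumed start delays and session rates). The illustrative artefact of 15% to 31% of the immediate gain rests on an assumed linear loss of 25% to 50% by 13 weeks and should not be read as a prediction. The primary T2 result is not in question.

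**What to change.** 1. State that randomised between-arm contrasts, including those from the secondary mixed models, are limited to T2.
2. Estimate retention as the T2-T3 and T1-T3 change within the intervention arm, each with a 95% CI. State that these are not randomised comparisons and cannot separate retention from disease progression or practice.
3. Replace the t test with control T2-T3 change against experimental T1-T3 change, labelled non-randomised and exploratory. Report each arm's actual time from last session to T3, because a mismatch of about 8 against 13 weeks remains.
4. Reconcile the Control Group phrase on completion of the project, and the Study Design phrase on the study period, with the passages that place control training after T2.

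The cost is wording only, plus reporting session dates that the trainer's log should already supply. No assessment is added. The price is giving up between-arm inference at T3, which the design does not support in any case.

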## Results

The study received ethical approval in July 2024 and recruitment started in January 2025. A graduate student, RA, and RC have been recruited and trained. Data collection began in February 2025, and the anticipated completion is February 2026.

## Discussion

### Overview

The need for improved manual wheelchair skills assessment and training in ARSACS and other neuromuscular disorders was observed and documented by our team. Given the strong documented evidence among heterogenous populations of adults [22,23], we hypothesize that an evidence-based standardized manual wheelchair skills training program will improve manual wheelchair skill performance for people with hereditary degenerative disorders such as ARSACS and MD1. This paper describes the protocol for a randomized waitlist controlled trial to evaluate the efficacy of the WSTP on manual wheelchair performance in adults with ARSACS or MD1 and explore the influence of training manual wheelchair skills capacity, manual wheelchair use self-efficacy, manual wheelchair mobility, and satisfaction with participation.

The United Nations declared mobility a basic human right [51]. For people with neuromuscular and hereditary degenerative disorders such as ARSACS and MD1, manual wheelchairs are commonly provided to facilitate self-directed mobility when walking becomes difficult or not possible. Similar to riding a bike, using a manual wheelchair requires skill development and practice over time in indoor and outdoor environments and during real-life situations. ARSACS and MD1 are highly prevalent in the province of Quebec, Canada. This geographic distribution has positioned our team to explore longitudinal aspects of mobility and participation in these 2 specific disorders, which may be generalized in the future to other neuromuscular disorders (eg, spinal muscle atrophy and muscular dystrophy).

Previous studies have documented the clinical significance of learning just one manual wheelchair skill, which could mean the difference between leaving the house independently to get groceries or relying on another person to complete this instrumental activity of daily living [27]. For example, learning how to do a transient tip (ie, popping the small front caster slightly off the ground to get over a door threshold, may make the difference between being able to leave the home or not). Once in the community, learning various approaches to opening heavy doors, maneuvering within small spaces, and navigating irregular surfaces and curbs may make the difference in being able to go to school independently, use public transit, participate in the workforce, or socialize with friends. Given that people with ARSACS have been shown to have very low manual wheelchair skills compared to other adult manual wheelchair users [16], this study has the potential to have major implications on mobility, participation in social and vocational activities, and quality of life for people with ARSACS and MD1.

Establishing the effect size in an RCT will position the research team to work with clinical partners to implement manual wheelchair skills training and evaluation into clinical practice. Given the proximity of the researchers and clinicians involved in this study (ie, the research center and rehabilitation center where outpatient services are provided are in the same building), this trial has the potential to catalyze change in manual wheelchair service provision for people with ARSACS and MD1. Implementing manual wheelchair skills training and evaluation into clinical practice would ensure that training starts early, specifically in the fundamental skills (eg, propulsion and maneuvering) and indoor skills that are required for getting around at home, school, and work. The training of various approaches needed for community and advanced skills (eg, ascending curbs and steep ramps) may be customized based on disease progression, manual wheelchair configuration, and personal experiences. This, in turn, could reduce risks of acute (eg, tips and falls) and overuse (eg, repetitive strain due to poor propulsion techniques) injuries [52-54]. Booster sessions may be provided to people on an as-needed basis, such as after accidents or changes in manual wheelchairs (a service covered by the provincial health care system in Quebec every 5 years). Moreover, optimizing manual wheelchair skills may reduce caregiver burden among those who assist with mobility to accomplish activities of daily living and social participation, roles that are commonly filled by parents, spouses, and other family members. Future studies may explore facilitators and barriers to implementing manual wheelchair skills evaluation into practice with clinicians and managers.

Finally, the collaborations with clinicians, a special interest group in neuromuscular disorders (Muscular Dystrophy Canada), and a citizen partner who has lived experiences with ARSACS and manual wheelchair training research will enhance the credibility of the research findings and increase the likelihood of successful future implementation. New research questions may be developed based on the needs identified by these groups.

A multifaceted knowledge translation strategy will be used to increase awareness and knowledge to change practice for manual wheelchair skills training for people with ARSACS and DM1. Targeted materials for health care professionals will include infographics, podcasts, and video capsules that will be launched through the international PROSPAX (Progression Chart of Spastic Ataxias) initiative on recessive ataxias and neuromuscular disorders ([name]), including Rare Disease Day. Materials will be shared through clinical and community platforms including websites and social media of Muscular Dystrophy Canada, Groupe de Recherche Interdisciplinaire sur les Maladies Neuromusculaires, and the Wheelchair Skills Program. Lunchtime presentations and manual wheelchair training workshops will be planned with clinicians. Academic dissemination will include a minimum of 2 peer-reviewed articles and 2 national/international conferences. Led by the corresponding author ([name]), all study investigators will have access to the final data set and will be eligible for authorship.

This study has limitations that should be considered. Although the sample size is powered for the primary outcome, we do not have the power to detect changes in secondary outcomes or for subgroup analysis to explore the influence of potentially confounding factors. Considering the population under study, there may be an increased risk of attrition due to fatigue or difficulty in scheduling training/testing sessions within the desired time frame. We hope to mitigate these issues by offering validated questionnaire versions of tests and by providing training in the community to overcome transportation challenges associated with commuting to a research center. Given that wheelchair configuration and positioning are outside the scope of the WSTP, we will not consider wheelchair configuration or positioning in this study. However, these factors may have an impact on manual wheelchair skill performance and capacity, and ultimately on the efficacy of the intervention.

